### Statistical analysis

Statistical analysis will be performed using SPSS Statistics Software 22.0 (IBM Corp., Armonk, NY, USA). For the results of the study, means ± standard deviations will be calculated for normally distributed quantitative variables and median (interquartile range) for non-normally distributed variables. In addition, the 95% confidence interval around the mean will be presented. For categorical variables, the number and percentage of patients within each category will be presented.

Statistical analyses of primary and secondary outcomes will be conducted as follows. First, all analyses will be based on the intention-to-treat (ITT) principle. All patients enrolled in the study will be included in the analyses, regardless of whether they complete the treatment or adhere to the protocol. Data distribution is expected to be normal, and skewed distribution data will be transformed prior to analysis. Then, the outcome of the clinical response will be analyzed by the c*hi*-squared test or Fisher’s exact test. For the secondary outcomes, repeated-measures analyses of variance (rANOVA) will be conducted to compare the changes in PSQI scores and the weekly dose of hypnotics at 8, 12, 16 and 20 weeks from baseline. Missing values will be addressed using the method of last observation carried forward (LOCF). To avoid potential confounding factors, additional sensitivity analyses will be performed following these statistical analyses.

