### Randomization and allocation concealment

Subjects will be randomly allocated into one of the two treatment arms in a 1:1 ratio: (1) treatment group (AA group) and (2) control group (SAA group). Central randomized allocation will be performed. Patients will be stratified based on six sites and randomly assigned to one of the two groups. The Chinese Clinical Trial Registry will generate the random number sequence using computer software, and will deposit the allocation sequence in ResMan^®^ Clinical Trial Management Public Platform, a web-based database. When a new participant is enrolled in the study, the research coordinator of each site will apply for the allocation information through this online system and assign participants to interventions accordingly. It is not possible to speculate on the allocation status of the participant before obtaining this information. The other personnel, including research nurses, assessors and clinical physicians, are not authorized to apply for random numbers. All processes will be recorded and saved appropriately.

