### Sample size estimation

In a pilot RCT conducted previously, the clinical response rates of AAT and sham AAT were 62.5% and 32.3%, respectively [22]. With these data, we used the following formula to calculate the estimated sample size [34].$$ \mathrm{N}\kern0.5em =\kern0.5em \frac{{\left({u}_{\alpha }+{u}_{\beta}\right)}^2\left(1+\raisebox{1ex}{$1$}\!\left/ \!\raisebox{-1ex}{$\mathrm{k}$}\right.\right)p\left(1-p\right)}{{\left({p}_e-{p}_c\right)}^2},\kern0.5em p\kern0.5em =\kern0.5em \frac{p_e+{kp}_c}{1+k} $$

In this formula, *k* (the ratio of allocation) = 1, *u*_a_ and *u*_*β*_ are 1.6449 and 1.2816, respectively, when 90% statistical power (*β* = 0.1) is required and a significance level of 5% (*α* = 0.05) is allowed. Here, *p*_e_ represents the incidence rate of the treatment group, while *p*_c_ represents that of the control group. Therefore, we will require at least 56 subjects in each group taking into account an allowed dropout rate of 15%. The results have been confirmed using PASS software 11.0 (NCSS, LLC, Kaysville, UT, USA) by tests for two independent proportions.

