### Outcome measurement

Sleep quality will be measured by PSQI score [35]. PSQI contains seven domains with scores from 0 to 3, yielding a total score ranging from 0 to 21, where a higher score indicates poorer sleep quality. The reliability and validity of its Chinese version have been confirmed [36, 37]. PSQI will be assessed at baseline, immediately after treatment (i.e., 8 weeks from baseline) and at 4, 8 and 12 weeks after treatment.

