#### Primary outcome measurement

The primary outcome will be the difference of the clinical response rates at 8 weeks from baseline between two groups. According to the academic literature review, response is defined as a reduction of PSQI global score ≥ 3 [38]. The clinical response rate will be the number of participants who achieve a reduction of PSQI global score exceeding 3 points divided by the total number of participants in each group and multiplied by 100%.

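### Site stratifies the randomisation and baseline PSQI is collected, but the named analyses use neither as a stratum or covariate, so precision is given up at no saving

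*Protocol article*

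**What the plan says.** On allocation, the Randomization and allocation concealment section of the protocol article states: "Patients will be stratified based on six sites and randomly assigned to one of the two groups". The ratio is 1:1. No block size or other device for balance within site is given.

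On data, the Outcome measurement section states: "PSQI will be assessed at baseline, immediately after treatment (i.e., 8 weeks from baseline) and at 4, 8 and 12 weeks after treatment". Inclusion requires a baseline global score above 7.

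On the primary endpoint, "response is defined as a reduction of PSQI global score ≥ 3". For its test, the Statistical analysis section reads "the outcome of the clinical response will be analyzed by the", and goes on to offer either a chi-squared or a Fisher's exact test. Score changes are handled separately, over the visits from week 8 to week 20: "repeated-measures analyses of variance (rANOVA) will be conducted to compare the changes in PSQI scores and the weekly dose of hypnotics". No site term and no baseline covariate is named for either analysis.

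The only other provision is: "To avoid potential confounding factors, additional sensitivity analyses will be performed following these statistical analyses". It names no variable and no model.

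**The concern.** When allocation is balanced within strata and the strata differ in outcome, the true variance of the treatment difference is smaller than an unstratified test assumes. The standard error is then too large and the test conservative. Site differences are plausible here: each centre has its own screener, nurses, coordinator and PSQI assessors, and the outcome is patient-reported.

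Baseline PSQI is a separate matter. Subtracting it, as both the responder definition and the change scores do, is not the same as adjusting for it. A covariate-adjusted comparison is at least as precise in large samples, and often clearly more so.

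At stake is precision in a trial of 112 patients, obtainable from variables already on file. The unnamed sensitivity analyses do not recover it, because they leave the primary result as it is.

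**Working it through.** **The plan's own figure.** Inputs from Sample size estimation: "the clinical response rates of AAT and sham AAT were 62.5% and 32.3%, respectively", quantiles 1.6449 and 1.2816, 15% dropout. With p = (0.625 + 0.323)/2 = 0.474,

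N = (1.6449 + 1.2816)² × 2 × 0.474 × 0.526 / (0.625 − 0.323)² = 8.564 × 0.4986 / 0.0912 = 46.8, so 47; 47/0.85 = 55.3, so 56 per group.

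The stated 56 is reproduced. Everything below is at two-sided 5%. The documents give no between-site spread, site sizes or correlations, so these are assumed and shown over a range.

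**Site, with allocation balanced within six sites, N = 112 (simulated, 20,000 to 40,000 trials).** CMH is the Cochran-Mantel-Haenszel test by site.

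| Site SD (logit) | Size, chi-squared | Size, CMH | Power, chi-squared | Power, CMH | Difference (points) |
|---|---|---|---|---|---|
| 0 | 4.54% | 4.63% | 89.62% | 89.68% | 0.06 |
| 0.3 | 4.42% | 4.73% | 90.25% | 90.61% | 0.36 |
| 0.5 | 4.17% | 4.99% | 90.49% | 91.56% | 1.07 |
| 0.75 | 3.40% | 5.05% | 91.15% | 93.38% | 2.23 |
| 1.0 | 2.62% | 4.76% | 92.02% | 95.11% | 3.09 |

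A separate simulation (40,000 trials, 9 to 10 patients per arm per site) gave sizes of 4.1% at SD 0.5 and 3.2% at SD 1.0 for chi-squared, with power rising under CMH from 90.4% to 91.3% and from 91.5% to 94.3%. The two agree on direction and order of size.

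Two readings matter. The chi-squared test is already at about 4.5% with no site effect, so only the gap below that is due to site. And if allocation is not balanced within site, chi-squared keeps its size: 5.0%, 5.0% and 4.9% at SD 0, 0.5 and 1.0.

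**Baseline PSQI as a covariate for response (20,000 trials).** Response is a threshold on a latent improvement correlated with baseline; the adjusted test is a linear model on the 0/1 outcome.

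| Correlation | 56 per arm: unadjusted | adjusted | Difference (points) |
|---|---|---|---|
| 0 | 89.84% | 89.88% | 0.04 |
| 0.3 | 89.44% | 91.19% | 1.75 |
| 0.4 | 89.92% | 92.84% | 2.92 |
| 0.5 | 89.53% | 93.86% | 4.33 |
| 0.6 | 89.80% | 95.74% | 5.94 |

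Type I error, checked at 47 per arm, was about 5% with and without adjustment.

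**Change scores at one visit.** Let r be the correlation of baseline with follow-up and k = baseline SD / follow-up SD. In units of the follow-up variance, a change score has variance 1 + k² − 2rk and a baseline-adjusted score has 1 − r². The ratio is

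(1 − r²) / (1 + k² − 2rk).

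With equal variances (k = 1) it reduces to (1 + r)/2, which is 0.65 at r = 0.3 and 0.85 at r = 0.7, a 15 to 35% smaller variance. If the entry rule narrows the baseline distribution, the gain shrinks:

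- k = 0.6, r = 0.4: 0.84 / (1 + 0.36 − 0.48) = 0.84/0.88 = 0.95.
- k = 0.7, r = 0.5: 0.75 / (1 + 0.49 − 0.70) = 0.75/0.79 = 0.95.

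The denominator equals (1 − r²) + (k − r)², so the ratio never exceeds 1 and the gain vanishes only when k = r.

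**The case against.** Several counter-arguments have force.

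- **Baseline is used.** Response is a fall from baseline and the ANOVA is of changes. This stands: what is missing is baseline as a covariate, and a claim that baseline is ignored would be wrong.
- **The error rate is not harmed.** A reader might infer that ignoring the strata misstates the error in a way that threatens a positive result. The documents do not support that. The only distortion is conservative, it concerns site alone, and it requires within-site balance, which the randomisation section does not state.
- **The site effect may be small.** All six centres are tertiary hospitals of Chinese Medicine in one province, and the nurses are trained in common. A low spread is plausible, and then the power at stake is at most about one point.
- **The trial is not underpowered because of this.** Unadjusted power at 56 per arm is already about 90%. The shortfall to about 85% at 47 per arm comes from the one-sided quantile in the sample size formula and is a different point.
- **Selective adjustment.** A reader might infer that covariates will be picked once the main results are known. The wording on sensitivity analyses gives an order of work, not a way of choosing models, so that charge does not hold.
- **Covariates belong in the analysis plan.** This has some weight for the repeated-measures ANOVA, for which the article lists no covariates. It has little for the primary outcome, where the article names a specific unstratified test.

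**Conclusion.** The point holds as a loss of precision. The article fixes a primary test that does not reflect its own stratification, and names no baseline covariate for either analysis.

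For site, the cost is about 0.3 to 1 point of power at an assumed SD of 0.3 to 0.5 and about 3 points at 1.0, provided that allocation is balanced within site. For baseline PSQI it is about 2 to 6 points for response at 56 per arm, at assumed correlations of 0.3 to 0.6. For change scores the variance forgone is 15 to 35% if baseline and follow-up variances are equal, but nearer 5% if the entry threshold strongly truncates baseline. False positives do not increase under any of these assumptions.

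The change is worth making because it is nearly free. A significant result from the plain test would still stand.

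**What to change.** Make the primary analysis a Cochran-Mantel-Haenszel test stratified by site, with the Mantel-Haenszel risk difference and its 95% confidence interval. Alternatively, use logistic regression with arm, site and baseline PSQI, reported as a standardised risk difference; this also captures the gain from baseline. Choose one in advance and keep the plain chi-squared test as supportive.

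State beforehand how small sites will be pooled: 112 patients over six sites average 9 to 10 per arm, and unequal recruitment could leave sparse strata.

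Include the baseline value of the outcome (PSQI score or weekly hypnotic dose) and site in the repeated-measures model.

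The Trial status section reports recruitment as ongoing, so on that status the wording can be settled before any analysis. Sample size, visits and data collection do not change. The cost is slightly more analysis work and the handling of sparse sites. If the analysis plan already contains these terms, the two documents need only be aligned.

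### LOCF scores anyone without a week-8 PSQI as a non-responder, which the dropout inflation does not reflect, and it fills the follow-up visits with earlier scores

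*Protocol article*

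**What the plan says.** Four parts of the protocol article bear on this.

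- **Outcome measurement** fixes the visits: "PSQI will be assessed at baseline, immediately after treatment (i.e., 8 weeks from baseline) and at 4, 8 and 12 weeks after treatment". No PSQI falls between baseline and week 8.
- **Primary outcome measurement** counts responders over everyone in the group.
- **Statistical analysis** analyses all enrolled patients by intention to treat, whether or not they complete, and adds: "Missing values will be addressed using the method of last observation carried forward (LOCF". The method for secondary endpoints is given as: "repeated-measures analyses of variance (rANOVA) will be conducted to compare the changes in PSQI scores and the weekly dose of hypnotics". The time points are weeks 8, 12, 16 and 20. The LOCF sentence is not limited to one endpoint.
- **Sample size estimation** starts from the pilot trial, where "the clinical response rates of AAT and sham AAT were 62.5% and 32.3%, respectively". It says "a significance level of 5% (*α* = 0.05) is allowed" and that the two normal quantiles "are 1.6449 and 1.2816, respectively, when 90% statistical power" is required. It arrives at 56 per group "taking into account an allowed dropout rate of 15" per cent.

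The Withdrawal criteria section says that the data of withdrawn participants will be collected and analysed. It does not say whether this includes a week-8 PSQI.

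**The concern.** For the primary endpoint, LOCF has only one value to carry. A patient with no week-8 PSQI receives the baseline score, so the change is exactly zero. That fails the response criterion whether the cut is read as at least 3 points or as more than 3 (the article words it both ways). Missing therefore means non-response, but the plan never says so, and the sample size is built on the opposite treatment of dropouts: it enlarges the groups and leaves the response rates untouched. That is right only if dropouts leave the denominator.

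Two things are at stake. The first is whether the stated 90% power belongs to the analysis that will be run. The second is the follow-up. Treatment ends at week 8, and change at each later visit is a secondary outcome. A carried score at weeks 12, 16 or 20 says nothing about what happened after the patient was lost, yet it enters the analysis as a measurement.

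**Working it through.** **Inputs.** Response rates 62.5% and 32.3%, quantiles 1.6449 and 1.2816, 15% dropout and 56 per group (Sample size estimation); "Subjects will be randomly allocated into one of the two treatment arms in a 1:1 ratio" (Randomization and allocation concealment).

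**1. The plan's own figure.** Mean rate p = (0.625 + 0.323)/2 = 0.474; difference 0.302.

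n = (1.6449 + 1.2816)² × 2 × 0.474 × 0.526 / 0.302² = 46.8, so 47 per arm. Then 47/0.85 = 55.3, so 56 per arm. The stated number reproduces exactly. The quantile 1.6449 is the one-sided 5% value.

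**2. Rates that LOCF would analyse.** Suppose a share d of each arm has no week-8 PSQI and the pilot rates are rates among completers (an assumption). All 56 stay in the denominator, so each rate is multiplied by (1 − d). At d = 0.15:

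- active: 0.85 × 0.625 = 0.531
- sham: 0.85 × 0.323 = 0.275
- difference: 25.7 points instead of 30.2

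**3. Power.** Power = Φ{ [Δ√n − z_α √(2p(1−p))] / √(p_e(1−p_e) + p_c(1−p_c)) }.

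Dropouts removed (56 × 0.85 = 47.6 per arm, undiluted rates), one-sided: (0.302 × 6.899 − 1.645 × 0.706)/0.673 = 1.370, power 91.5%.

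Dropouts kept as non-responders (56 per arm, diluted rates; p = 0.403), one-sided: (0.2567 × 7.483 − 1.645 × 0.694)/0.669 = 1.165, power 87.8%. Exact enumeration of the chi-squared test gives 87.9%.

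| Loss before week 8, equal in both arms (assumed) | One-sided, removed | One-sided, LOCF | Two-sided, removed | Two-sided, LOCF |
|---|---|---|---|---|
| 5% | 93.9% | 92.9% | 88.8% | 87.3% |
| 10% | 92.8% | 90.6% | 87.1% | 83.8% |
| 15% | 91.5% | 87.8% | 85.1% | 79.9% |
| 20% | 89.9% | 84.7% | 82.8% | 75.7% |

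At 15% loss, LOCF costs 91.5 − 87.8 = 3.7 points one-sided, or 85.1 − 79.9 = 5.2 points two-sided. With the diluted rates, the plan's own formula needs 62.5, so 63 per arm, for 90% power one-sided.

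**4. Unequal loss (assumed splits, 56 per arm).**

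- 20% lost on active and 10% on sham: rates 50.0% vs 29.1%; power 73.7% one-sided, 62.3% two-sided.
- 10% on active and 20% on sham: rates 56.3% vs 25.8%; power 95.6% and 91.6%.
- No true effect (47.4% response in both arms) with 10% vs 20% loss: rates 42.7% vs 37.9%. A two-sided 5% test then favours the arm with less loss about 7.3% of the time, against a nominal 2.5% in that direction.

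**5. Follow-up.** Let g be the share lost before week 8 and f the share lost after week 8 but before week 20, equal in both arms. Let D8 and D20 be the true differences in mean PSQI change, the same for lost and retained patients. LOCF estimates at week 20

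(1 − f − g) × D20 + f × D8 + g × 0,

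so the bias is f × (D8 − D20) − g × D20. If all 15% is lost after week 8 and the effect has gone by week 20, the bias is +0.15 × D8, a false lasting benefit. If all 15% is lost before week 8 and the effect persists, it is −0.15 × D20, a lasting benefit understated. The documents give no split of the 15% and no PSQI standard deviation, so this cannot be turned into points on the scale.

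**The case against.** **The power loss is small in the plan's own terms.** This stands. About 88% against a target of 90% is a modest shortfall, and at 10% loss there is none. A reader might infer that LOCF takes power from 90% to 80%. The documents do not support that: two-sided power is already 85.1% at 15% loss with dropouts simply removed. The gap from 90% to 85% comes from the one-sided quantile, which is a separate matter.

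**The dilution may already be in the pilot rates.** This stands as a limit. The pilot chi-squared of 5.77 (Background) is what 20/32 against 10/31 gives, but nothing says whether those were all randomised patients or only completers. If dropouts were already counted as failures, multiplying by 0.85 counts them twice. Power at 56 per arm would then be 94.9% one-sided and 90.3% two-sided, with no loss.

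**The denominator already implies non-response, and withdrawn participants' data are to be collected.** Both are partly right. Stating non-response openly leaves the primary result unchanged, and a patient who stops acupressure but is assessed at week 8 is unaffected. What remains is that the power does not match the rule, and that the collection sentence does not say whether the scheduled PSQI is included.

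**LOCF overstates durability.** A reader might infer this as a general result. It follows only where losses come after week 8 and the effect fades, since earlier losses carry baseline and pull the other way. Nor can the single 15% allowance be placed wholly before week 8 for the primary endpoint and wholly after it for the follow-up. The article also gives no reason for choosing LOCF, so none should be attributed to it.

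**Conclusion.** The point holds in a limited form. ITT with LOCF makes every patient without a week-8 PSQI a non-responder, while the sample size treats dropouts as absent. If the pilot rates are completer rates and the full 15% is lost before week 8, equally in both arms, power is about 88% one-sided rather than 90%. It stays above 90% at 10% loss, and there is no dilution if the pilot rates already counted dropouts as failures. Unequal loss matters more, because it can move the primary comparison in either direction. In follow-up, carried scores are treated as observed, which hides uncertainty and biases weeks 12 to 20 in a direction that cannot be fixed in advance. This should be corrected, but it does not undermine the trial.

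**What to change.** 1. **Primary outcome.** Replace LOCF by an explicit rule that a missing week-8 PSQI counts as non-response. Restate power under that rule over a range of loss before week 8, as in the table, and say whether the pilot rates are completer rates. Add multiple imputation as a sensitivity analysis, so that unequal loss can be examined.
2. **Secondary outcomes.** Replace rANOVA with LOCF by a linear mixed model for repeated measures on all observed visits, with arm-by-visit terms and a contrast at each visit. The MIXED procedure in SPSS, the package already named, can fit it.
3. **Data collection.** Make explicit that the data to be collected from withdrawn participants include the scheduled PSQI assessments after treatment stops, where the participant consents. The withdrawal rule itself stays as it is.

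The cost is slightly more analysis work, continued use of a questionnaire already scheduled, and a slightly less favourable stated power. Recruitment is described as ongoing, so the wording can still be settled before analysis.

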## Discussion

Impaired sleep quality of patients on dialysis adversely impacts their quality of life and long-term survival. Although AAT has been practiced as a complementary treatment for insomnia, there is still an important gap with regard to sufficient evidence. The results of this trial are expected to provide convincing evidence regarding whether AAT is effective for MHD patients with insomnia.

This study has been designed carefully following the Consolidated Standards of Reporting Trials (CONSORT) Statement of RCTs and reported according to the Standard Protocol Items: Recommendations for Interventional Trials (SPIRIT) Statement (Additional file 1). One of the major issues in the trial design is the setting of the control group. Studies on the efficacy of acupuncture have been controversial based mainly on the following two points: first, the psychological effect (placebo effect, from both the investigators and the patients) could make a considerable contribution to the results. Second, the therapeutic effect may not depend on specific points. Our previous pilot study showed that points on the helix, which are irrelevant to the physiology of sleep, are appropriate for the sham intervention. In addition, we specified the points in both groups as numbers and letters. We also scripted the interactions between practitioners/assessors and subjects. These approaches help to blind both the participants and the practitioners, reducing their psychological interference to the minimum. Therefore, it will be easier to interpret the contributions of specific acupoints to the outcome.

Another concern is whether hypnotics should be washed out and prohibited during the trial. Indeed, this approach is good for trial design but impractical for carrying out the trial, because it increases the suffering of patients and reduces their compliance. As the trial is intended to assess whether AAT can help improve sleep quality and reduce drug use, rather than whether AAT is better than hypnotics, we decided to allow the use of hypnotics under conditions of strict surveillance.

For outcome measurement, PSQI is a well-validated, patient-reported questionnaire. But for now there is not a defined minimal clinically important difference (MICD) to reflect the changes in a clinical intervention that are meaningful for the patients. In some case, statistically significant difference has little clinical significance. Therefore, we adopted the response rate for the primary endpoint from a clinical trial published by [name], the author of the PSQI. He performed a comprehensive data review to set the criteria for response: participant with a change in PSQI of more than 3 points after treatment was defined as a response case [38]. In addition, the global PSQI score and scores of seven domains will be also analyzed as secondary outcomes in this trial.

The design of the trial minimizes the risk of bias by the following methods: (1) It is designed as a multi-center, double-blinded RCT. A central randomization method is applied to ensure completely random allocation and concealment. Both the patients and the assessors are blinded to the groups, (2) The sample size was estimated based on a previous pilot study [22], (3) The screening of participants is performed strictly to represent the population studied, (4) The manipulation of AAT is standardized and the practice of AAT is performed strictly under the guidance of authoritative clinical guidelines [40, 41]. A senior acupuncturist will be invited to train the research nurses from six sites and assess their competence, which will ensure the homogeneity of treatment and (5) The selected scale for outcome measurement is of good validity and reliability [42]. The investigators involved in the study will undergo a training course and have their role assigned clearly before the start of the trial.

There are several limitations of this study. First, sleep quality is not assessed by objective measurement such as polysomnography or actigraphy. There are some difficulties for us to perform these tests. Most hemodialysis patients refused to go through polysomnography in our pilot studies when they were required to stay a whole night in hospital. Actigraphy seems easily accepted but this equipment is unavailable in all centers. Due to limited financial support, we have to make the best of a well-acknowledged scale to assess the outcome. In a future study, actigraphy should be included. Second, anxiety and depression are commonly accompanied with sleep disorders but are not assessed in this study. Recent study has suggested that they have positive correlations with PSQI score [43]. A more comprehensive assessment of the effect of auricular acupressure will include sleep quality, anxiety and depression, and quality of life in future study.

This protocol offers a standardized process to guide subsequent clinical research. The results of this trial will generate concrete evidence regarding the efficacy of AAT in insomnia management of dialysis patients.

